## 10.2. Specifications of Exploratory Endpoints Analyses

### 10.2.1. Definitions and Derivations

- Age (years) will be collected from the “Demography” Page of Case Report Form (CRF).
- Smoking history will be collected from the “Smoking and Alcohol History” Page of CRF.

- History of diabetes, hypertension, hyperlipidemia, and previous history of surgery on the radial artery will be collected from the “Prior Medical History” Page of CRF.
- Type III aortic arch configuration, Development status and degree of tortuosity of the aortic arch and arch vessels will be collected from the “Details of the Angiographic Procedure” Page of CRF.
- Diameter of the radial artery will be collected from the “Details of Preoperative Imaging Examination” Page of CRF.
- Development status of the radial artery will be collected from the “Radial Artery Development Assessment” Page of CRF.

### 10.2.2. Analysis Methods

- If data permit, a generalized linear regression with stepwise selection of covariates will be used to conduct an exploratory analysis of factors affecting cerebral angiography through TRA approach.

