**Success rate of diagnostic cerebral angiography**

Successful diagnostic angiography: the aortic arch vessel is successfully selected without changing the puncture site, with angiography results meeting the diagnostic requirements.

For intraoperative management, please refers to *Chinese Expert Consensus on Good Practice for Cerebral Angiography (2018)*.

In case of angiography failure, record in which of the following stages it occurs and why it occurs:

Stage 1: Unable to insert the arterial sheath (small artery diameter, no blood return after arterial puncture, unable to advance the guidewire due to vasospasm, and atherosclerotic plaque, etc.);

Stage 2: Puncture and sheath placement is successful, but the catheter or guidewire cannot be advanced (arterial tortuosity, vasospasm, and loop, etc.);

Stage 3: The guidewire and catheter has reached the aortic arch, but the primary branch of the aortic arch cannot be selected;

Stage 4: The guidewire and catheter has reached the primary branch of the aortic arch, but the procedure still cannot be completed successfully;

➤ **Secondary Effectiveness Endpoints:**

- Success rate of accurate diagnosis: successful accurate diagnosis is defined as the responsible vessel for the disease is successfully superselected without changing the puncture site, with angiography results meeting the diagnostic requirements.
- Duration of angiography: Time from puncture to the end of the angiography.
- Duration of fluoroscopy: Data from the machine will be used.
- Bedridden time: Time (hours) from the end of the procedure to ambulation.
- Visual Analogue Scale (VAS) score: The VAS will be completed within 24 hours after the end of the angiography. The VAS is provided in Appendix 3.

(2) Safety Endpoints:

- Incidences of angiographic complications during and within 24 hours after the procedure
- Incidences of major angiographic complications during and within 24 hours after the procedure

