### **7.3 Sample Size Estimation**

This study will test the hypothesis that the success rate of diagnostic cerebral angiography by TRA approach is not inferior to that by TFA approach.

We assume the success rates of diagnostic cerebral angiography by TRA and TFA are 97% and 98% respectively by considering the data in the references, with a margin for non-inferiority of -5%, a power of 90% at one-side significance level of 0.025, and a drop-out rate of 10%, 429 cases are needed for each group according to PASS 15 software, and thus a total of 858 subjects need to be enrolled in this study.

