### **7.7.3 Exploratory Analysis**

If data permit, Logistic regression will be used to conduct an exploratory analysis of factors affecting cerebral angiography through TRA approach. Influencing factors may include age, diabetes, hypertension, hyperlipidemia, smoking history, Type III aortic arch configuration, looping technique, diameter and development status of the radial artery, development status of the aortic arch and arch vessels and degree of tortuosity, previous history of surgery on the radial artery.

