## 3. Sample Size Considerations

This study will test the hypothesis that the success rate of diagnostic cerebral angiography by TRA approach is not inferior to that by TFA approach.

The success rates of diagnostic cerebral angiography by TRA and TFA are assumed to be 97% and 98% respectively. With a margin for non-inferiority of -5% and a drop-out rate of 10%, 429 cases are needed for each group to achieve a power of 90% at one-sided significance level of

0.025, according to PASS 15 software, and thus a total of 858 subjects need to be enrolled in this study.

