### 10.2.3. Model Specifications

| Statistical Analysis of Exploratory Variables                                                                                                                                                                         |                          |
|-----------------------------------------------------------------------------------------------------------------------------------------------------------------------------------------------------------------------|--------------------------|
| Endpoints and Parameters                                                                                                                                                                                              |                          |
| 
 
• Endpoints: successful/ failed cerebral angiography through TRA approach
 
• Parameters: 
 
– RR and 95% CI
 
 
 
 |                          |
| Input Variables                                                                                                                                                                                                       |                          |
| 
 
• AVAL: Response variable
 
• COVARIATES: Influencing factors
 
                                                                                                |                          |
| Sample SAS code                                                                                                                                                                                                       |                          |
| 
Generalized linear regression sample code:
 <pre>PROC GENMOD DATA=adeff;   CLASS TRTPN;   MODEL AVAL = COVARIATES / DIST=BIN LINK=LOG   SELECTION=STEPWISE;   RR COVARIATES / CL;</pre>                  |                          |
| QMS Document Name: Statistical Analysis Plan Template(EN)                                                                                                                                                             | Page 30 of 38            |
| QMS No (include version ref): STF-015-GL.03                                                                                                                                                                           | Document date: 14JUL2022 |

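### The TRA factor analysis applies stepwise log-binomial selection to about 13 failures and 15 or more factors, does not say which outcome is modelled, and can lose early failures from any model using arch variables.

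*Combined protocol and SAP*

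**What the plan says.** Protocol 2.1 gives the analysis of factors affecting TRA angiography as the only secondary objective. Protocol 7.7.3 plans the method, provided the data allow it: "Logistic regression will be used to conduct an exploratory analysis of factors affecting cerebral angiography through TRA approach".

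The SAP treats the analysis as exploratory. Section 10.1 restricts it to the TRA group of the FAS, and Table 7 asks for univariable results and then multivariable results with stepwise selection. Section 10.2.2 says that "a generalized linear regression with stepwise selection of covariates will be used to conduct an exploratory analysis", again only if the data allow, and the sample code in 10.2.3 reads "MODEL AVAL = COVARIATES / DIST=BIN LINK=LOG". No entry or stay level, cap on terms, minimum number of failures or fallback for a failed fit is given.

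Table 7 takes its factors from the subgroup list in SAP 8.3. SAP 1.2 and 10.2.1 name others that 8.3 does not list: radial artery diameter, radial development status and radial surgery history, plus looping technique in 1.2.

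On data sources, SAP 10.2.1 states: "Type III aortic arch configuration, Development status and degree of tortuosity of the aortic arch and arch vessels will be collected from the" CRF page for the angiographic procedure. Protocol Appendix 1, note e, limits screening imaging to the extremities. SAP Appendix 3 rules out imputation. Protocol 2.2 grades failures by stage, beginning with "Stage 1: Unable to insert the arterial sheath"; at Stage 2 the sheath is in but the catheter or guidewire cannot be advanced.

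**The concern.** Three features combine badly.

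- **Too few events.** Success is expected in nearly every patient, so the information lies in a handful of failures, and stepwise selection searches a list longer than the number of failures. Selected factors will often be chance findings with inflated effects.
- **A fragile model with an unstated outcome.** A log-link binomial model must keep every fitted probability at or below 1. That is hard when success near 97% is modelled and much easier when failure near 3% is modelled. The primary GENMOD code in SAP 8.1.2.3.1 has DESCENDING; the exploratory code does not. If the outcome is coded the same way, the two calls model opposite levels. Table 7 does not settle it, since it describes a risk ratio between successful and failed groups.
- **Missingness tied to the outcome.** A success has by definition had the arch vessel selected, whereas a Stage 1 or 2 failure has not reached the arch by the assigned route. Structural loss of arch variables can therefore affect failures only.

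At stake is a published list of risk factors for TRA failure that may be largely noise and may miss the radial-access causes that the protocol itself lists for early failure.

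**Working it through.** **Inputs.** "The success rates of diagnostic cerebral angiography by TRA and TFA are assumed to be 97% and 98% respectively" (SAP 3). "With a margin for non-inferiority of -5% and a drop-out rate of 10%, 429 cases are needed for each group" (SAP 3), for "a power of 90% at one-side significance level of 0.025" (protocol 7.3). SAP 8.3 has 14 bullets, the last joining two factors, so 15 factors, three of them about the arch.

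**The plan's own figure.** 429 × 0.9 = 386 evaluable per arm, and 386 / 0.9 = 428.9, rounded up to 429. Exact binomial enumeration at 386 per arm gives 90.5% power for the continuity-corrected Z test, so 429 reproduces. The documents state no expected number of failures.

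**Failures per factor.**
- n = 429: 429 × 0.03 = 12.9 failures (binomial 95% range 6 to 20); 12.9 / 15 = 0.86 per factor.
- n = 386: 386 × 0.03 = 11.6 failures (range 6 to 19); 11.6 / 15 = 0.77 per factor.

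**Model behaviour.** The simulation used 200 trials per setting, n = 429 and complete data. It assumed 15 independent covariates (4 continuous, 11 binary with prevalences of 10% to 60%) and forward selection at p < 0.05. Ranges cover settings with and without true effects.

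| | Failure modelled | Success modelled |
|---|---|---|
| Full 15-factor model fits properly | 40–45% | 0% |
| Single-factor model fits properly | 96–97% | 88–89% |
| Selection run meets at least one bad fit | 46–49% | 93–96% |
| At least one factor selected, no true effects | 45% | 56% |

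A separate check, screening each factor by a logistic Wald test, gave about 36% for the last row at n = 429. The range across methods is therefore about 36% to 56%.

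**Exaggeration.** With failure modelled and no missing data, an arch factor with a true failure RR of 2 averaged an RR of 4.3 in the trials where it reached p < 0.05.

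**Loss of early failures.** The documents give no split by stage, so the early share s is assumed.
- Failures left of 12.9: 12.9 × (1 − s) = 9.7, 6.4 and 3.2 for s = 25%, 50% and 75%. In simulation, with failure modelled, the full model then fitted in 32%, 12% and 0% of trials.
- Take a radial factor with 30% prevalence that triples early failure only. With e = 0.03s and l = 0.03(1 − s), e0 = e / (0.7 + 0.3 × 3) and e1 = 3 × e0. The true overall RR is (e1 + l) / (e0 + l); the complete-case RR is (1 − e0) / (1 − e1). At s = 50%, e0 = 0.0094, e1 = 0.0281 and l = 0.015, giving a true RR of 1.77 and a complete-case RR of 1.02. At s = 25% and 75%, true RRs of 1.34 and 2.30 become 1.01 and 1.03.
- Arch subgroups: 429 patients with 13 failures leave 416 successes. If k failures have no arch data, pooled success across the subgroups is 416 / (429 − k) instead of 416 / 429 = 96.97%. For k = 3, 6 and 10 this gives 97.65%, 98.35% and 99.28%, an overstatement of 0.7, 1.4 and 2.3 points.

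**The case against.** The analysis is labelled exploratory, runs only if the data allow, and cannot touch the primary conclusion. The long factor list comes from the protocol's logistic plan, not from the change of link. All of that stands and limits the weight of the point.

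Several stronger readings are tempting, and the documents do not support them.

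- *That the model will rarely fit.* This is so for the full model if success is modelled, or if half or more of the failures lack arch data. With failure modelled and complete data, 40% to 45% of full models and nearly all single-factor models fit. Leaving out DESCENDING may even mean that failure is intended.
- *That the risk ratio for success cannot exceed 1.03.* The bound is 1 divided by success in the reference group, not overall success. With 90% in the reference group it is 1 / 0.90 = 1.11.
- *That the SAP misapplied its stated reason for moving from OR to RR.* Table 1 gives that reason only in the row on the primary endpoint. For the exploratory analysis no reason is given, so the defect is an undocumented change.
- *That every early failure is lost.* Eligibility requires suitability for both routes, and SAP Table 4 tabulates failures with crossover. A patient who crosses over may have the arch imaged and recorded; the documents do not say. Models without arch factors are not affected.

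The SAP also reports a missing category for categorical variables (SAP 6) and by default keeps missing observations in denominators (SAP Appendix 2). Descriptive tables would therefore reveal missing arch data, but this does not return those patients to a regression or to an arch subgroup.

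**Conclusion.** The concern holds in this form. With about 12 to 13 expected failures and 15 or more candidates, stepwise log-binomial selection will often choose factors by chance, exaggerate those it chooses, and often fail to fit in full. The failure count rests on the planned 97% success; even at the upper limit of 20 failures there would be only 20 / 15 = 1.3 per factor. The fit and selection percentages rest on independent covariates with assumed prevalences, and they depend on the modelled level, which the SAP must state.

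Outcome-dependent loss follows from the data sources, but its extent is unknown. It covers only Stage 1 or 2 failures without recorded arch data, and only analyses that use arch variables. The figures of 0.7 to 2.3 points are a range over assumed losses, not a prediction.

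The non-inferiority result is unaffected. The change is still worth making, because this analysis answers the protocol's only stated secondary objective.

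**What to change.** Amend SAP 10 and 8.3 before database lock:

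1. State that failure is modelled, and give the coding.
2. Replace the stepwise log-binomial model with Firth-penalised logistic regression, which returns to the protocol's method in a form suited to few events. If a log link is kept, record the change and its reason in Table 1.
3. Remove stepwise selection. Prespecify a joint model of two or three factors, and report the others as univariable odds ratios with penalised-likelihood confidence intervals.
4. Settle one candidate list across SAP 1.2, 8.3 and 10.2.1, and state the minimum number of failures at which the joint model will be run.
5. Take arch variables from the crossover angiogram where there is one. Otherwise show the patient as arch not reached in the arch subgroups, and keep these patients in all models of non-arch factors. Report the number by stage.

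The cost is SAP wording and code, with no added patients. The joint model has fewer factors, and the exploratory results are odds ratios, not risk ratios. Firth's method is one of several workable choices; the essential parts are the stated outcome, the short prespecified list and the handling of missing arch data.

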### 10.2.3. Model Specifications

| Statistical Analysis of Exploratory Variables                                                                                                                                                                         |                          |
|-----------------------------------------------------------------------------------------------------------------------------------------------------------------------------------------------------------------------|--------------------------|
| Endpoints and Parameters                                                                                                                                                                                              |                          |
| 
 
• Endpoints: successful/ failed cerebral angiography through TRA approach
 
• Parameters: 
 
– RR and 95% CI
 
 
 
 |                          |
| Input Variables                                                                                                                                                                                                       |                          |
| 
 
• AVAL: Response variable
 
• COVARIATES: Influencing factors
 
                                                                                                |                          |
| Sample SAS code                                                                                                                                                                                                       |                          |
| 
Generalized linear regression sample code:
 <pre>PROC GENMOD DATA=adeff;   CLASS TRTPN;   MODEL AVAL = COVARIATES / DIST=BIN LINK=LOG   SELECTION=STEPWISE;   RR COVARIATES / CL;</pre>                  |                          |
| QMS Document Name: Statistical Analysis Plan Template(EN)                                                                                                                                                             | Page 30 of 38            |
| QMS No (include version ref): STF-015-GL.03                                                                                                                                                                           | Document date: 14JUL2022 |
| CONFIDENTIAL                                                                                                                                                                                                          |                          |

|                                                                                                                        |
|------------------------------------------------------------------------------------------------------------------------|
| ODS OUTPUT ParameterEstimates=RRResults;
RUN;                                                               |
| Results Presentation                                                                                            |
| 
 
The RR and 95% Wald CI for the ratio can be obtained from RRResults.
 
 |

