| Body height (cm)                                                                                                               |                         |        |         |
| Baseline BMI (kg/m  )                                                                                              |                         |        |         |
| Modified Rankin Scale (mRS) score                                                                                              |                         |        |         |
| Smoking history                                                                                                                |                         |        |         |
| Alcohol history                                                                                                                |                         |        |         |
| Prior Medical History                                                                                                          |                         |        |         |
| Diabetes (Yes/ No/ Unknown)                                                                                                    | Y                       |        | Y       |
| Type of Diabetes (Type I/ Type II/ Other)                                                                                      |                         |        |         |
| Hypertension (Yes/ No/ Unknown)                                                                                                |                         |        |         |
| Hyperlipidemia (Yes/ No/ Unknown)                                                                                              |                         |        |         |
| Coronary Heart Disease (Yes/ No/ Unknown)                                                                                      |                         |        |         |
| Type of Coronary Heart Disease (Acute Myocardial Infarction /Old Myocardial Infarction /Unstable Angina/ Stable Angina/ Other) |                         |        |         |
| Cerebrovascular Disease (Yes/ No/ Unknown)                                                                                     |                         |        |         |
| Type of Cerebrovascular Disease (Ischemic/ Hemorrhagic/ Mixed/ Other)                                                          |                         |        |         |

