#### Generalized linear regression sample code:

```
PROC GENMOD DATA=adeff DESCENDING;
```

|                                                                                                                                                                                                                                                                                                                                                   |
|---------------------------------------------------------------------------------------------------------------------------------------------------------------------------------------------------------------------------------------------------------------------------------------------------------------------------------------------------|
| CLASS TRTPN AVAL;
MODEL AVAL = TRTPN / DIST=BIN LINK=LOG;
where paramcd='DCA';
ESTIMATE 'Risk Ratio for TRTPN' TRTPN 1 -1 / EXP;
ODS OUTPUT Estimates=RRCL;
RUN;                                                                                                                         |
| Results Presentation                                                                                                                                                                                                                                                                                                                       |
| 
 
• Rate estimate and 95% CI can be retained from BinomialCL.
 
• Rate difference and 95% CI can be retained from diff.
 
• P value of non-inferiority test can be retained from noninf.
 
• Risk Ratio between TRA and TFA groups and its 95% CI can be retained from RRCL.
 
 |

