| Generalized linear regression: risk ratio (RR) between successful and failed diagnostic cerebral angiography groups using TRA approach and its 95% CI 
 
Univariable results
 
Multivariable results with stepwise selection
 
 | Y                       |        | Y       |

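### SAP 10.2.3 takes the risk ratios for factors affecting TRA from a log-scale coefficient table without exponentiating, and Table 7 defines the ratio differently from the model

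*Combined protocol and SAP*

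**What the plan says.** SAP 10.2.3 names the outcome as "Endpoints: successful/ failed cerebral angiography through TRA approach" and the inputs as "COVARIATES: Influencing factors". The model line is "MODEL AVAL = COVARIATES / DIST=BIN LINK=LOG", with stepwise selection requested. The only CLASS variable is `TRTPN`. The output is captured by "ODS OUTPUT ParameterEstimates=RRResults", and under Results Presentation the SAP states: "The RR and 95% Wald CI for the ratio can be obtained from RRResults".

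Table 7 (SAP 10.1) describes the same result as "risk ratio (RR) between successful and failed diagnostic cerebral angiography groups using TRA approach and its 95% CI".

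The log-link model for the primary endpoint (SAP 8.1.2.3.1) is handled differently. It contains "ESTIMATE 'Risk Ratio for TRTPN' TRTPN 1 -1 / EXP", reads the ratio from the Estimates output, uses `DESCENDING`, and filters on `paramcd='DCA'`. None of these appears in the 10.2.3 code.

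SAP 10.1 bases the exploratory analyses on the TRA group of the FAS. Some candidate factors have more than two recorded categories. Table 3 lists "Diabetes (Yes/ No/ Unknown"), with the same pattern for hypertension and hyperlipidemia, and SAP 8.3, to which Table 7 refers, includes aortic arch classification.

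**The concern.** The SAP gives two rules for reading a risk ratio from a log-link model, and only the one in 8.1.2.3.1 yields a ratio. On the log scale no effect is 0; on the ratio scale it is 1. A log-scale interval lying wholly above 0 can include 1, so a clear association can be misread as none.

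Table 7 and 10.2.3 also describe different quantities. A ratio between successful and failed groups compares how common a factor is in each outcome group. A model with the outcome as response compares the risk of that outcome between levels of the factor.

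The TRA factors are the only secondary objective in protocol 2.1, so the reported ratios should be what their label says.

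**Working it through.** **Inputs.** From the SAP: binomial distribution, log link, TRA group only, read-out from `ParameterEstimates`. From the sample size section: 429 per group, 10% drop-out, 97% TRA success. That gives 429 × 0.9 ≈ 386 evaluable TRA subjects and 386 × 0.03 ≈ 12 failures. The split of failures by factor is assumed, because the documents give none. Software assumption: `ParameterEstimates` holds coefficients and Wald limits on the link scale.

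**1. Read-out rule.** Assume 7 of 77 subjects with a type III arch fail and 5 of 309 others fail (386 subjects, 12 failures).

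- RR of failure = (7/77)/(5/309) = 0.0909/0.0162 = 5.62.
- Coefficient = ln(5.618) = 1.726.
- SE = √(1/7 − 1/77 + 1/5 − 1/309) = √0.3266 = 0.5715.
- Wald limits on the log scale = 1.726 ± 1.96 × 0.5715 = 0.606 to 2.846.
- Exponentiated: 5.62 (1.83 to 17.2).

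| Read-out | Printed as RR | 95% limits |
|---|---|---|
| As 10.2.3 states | 1.73 | 0.61 to 2.85 |
| Exponentiated, as in 8.1.2.3.1 | 5.62 | 1.83 to 17.2 |

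The first row looks like an ordinary risk ratio whose interval includes 1. The second excludes 1.

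If success is modelled, RR = (70/77)/(304/309) = 0.924 and the coefficient is −0.079. A negative number cannot be a ratio, so that version would be noticed. The 10.2.3 code does not state which event is modelled. If `AVAL` is coded 0/1 and the software takes the lower value by default (assumption), failure is modelled, and the error is then harder to see.

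**2. Table 7 against 10.2.3.** On the same counts, the prevalence of type III arch is 70/374 = 18.7% among successes and 7/12 = 58.3% among failures. The ratio between those groups is 0.187/0.583 = 0.32. The model's ratio is 5.62 for failure or 0.924 for success. The three figures answer different questions.

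**3. CLASS (secondary).** `TRTPN` is constant in a TRA-only set, and no factor is listed. A two-level factor gives the same ratio between its two levels with or without CLASS, provided the codes are one unit apart. A continuous factor needs no entry. A numerically coded factor with three or more levels would be fitted as a straight line on the log scale. Two illustrations, each with 386 subjects and 12 failures:

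- Three ordered levels, failures 2/186, 6/120, 4/80. Categorical RRs against level 1: 0.05/0.01075 = 4.65 for both. Linear score: 1.95 per step, which implies 3.80 for level 3 against level 1.
- Yes/No/Unknown scored 1/2/3. With Yes 6/100, No 4/226 and Unknown 2/60, the Yes-to-No RR is 0.06/0.0177 = 3.39 and the linear score gives 1.81. With Yes 6/100, No 6/276 and Unknown 0/10, the RR is 2.76 and the linear score gives 2.86.

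The distortion depends on the coding and on the size of the Unknown cell. The documents give neither.

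**The case against.** The strongest reply is that this is labelled sample code with a placeholder for the covariates, and that it would not run as printed: an RR statement and stepwise selection are not part of this procedure (software assumption). A programmer would have to rewrite it, the SAP plainly intends ratios, and a negative coefficient would expose the mistake. Much of this stands. A reader might infer that the reported figures are certain not to be risk ratios. The documents do not support that, because the error arises only if the code is repaired and the read-out rule is kept. But that rule is a sentence of SAP text under Results Presentation, and Table 7 is not code either. A repair of syntax alone leaves both in place.

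A second reply is that Table 7 is only a row label and that no method in the SAP computes a ratio of prevalences. That is fair. It makes this a contradiction to reconcile, and the 0.32 above is not a likely result.

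A third concerns the linear scores. A reader might infer that categorical factors will be modelled that way and that a strong factor could look null. One can build such a case: Yes 6/100, No 4/226, Unknown 4/60 turns 3.39 into 1.11. But it has 14 failures, more than the 12 expected, and puts 60/386 = 15.5% of subjects in Unknown, with more failures there (6.7%) than in Yes (6.0%). Nothing in the documents supports those cells. Character-coded factors would be expected to stop the run rather than fit a line.

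**Conclusion.** The point holds in limited form. Followed as written, SAP 10.2.3 reports log(RR) and log-scale limits as RR and its 95% CI; in the illustration, 1.73 (0.61 to 2.85) in place of 5.62 (1.83 to 17.2). Table 7 contradicts the response and covariates set out in 10.2.3. The CLASS omission matters only for factors coded numerically with three or more levels, and its size cannot be determined from the documents.

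The figures rest on assumed cell counts, on about 386 evaluable TRA subjects with 12 failures, and on the software assumptions stated above.

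The severity is minor. Although the factors are the secondary objective in protocol 2.1, protocol 7.7.3 and SAP 10.2.2 make the analysis exploratory and conditional on the data permitting it, and about 12 failures may not permit it. A reader might infer from the protocol objective that a main conclusion is at risk. It is not: the primary code exponentiates its ratio, and the non-inferiority test does not use this model.

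**What to change.** In SAP 10.2.3:

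- Report exp(Estimate) and the exponentials of the two Wald limits, or use ESTIMATE with EXP as in 8.1.2.3.1, and change the Results Presentation sentence to match.
- Delete the RR statement, and name a procedure that carries out the stepwise selection if it is kept.
- Replace `CLASS TRTPN` with the categorical factors and their reference levels. State whether Unknown is treated as missing or as its own level.
- State the modelled event, for example through `DESCENDING` or `EVENT=`.
- Restrict the data to the TRA arm and to `paramcd='DCA'`.

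In Table 7, define the ratio as the risk of the stated outcome in subjects with the factor divided by that risk in subjects without it, or in the reference level.

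The cost is a few lines of SAP text and code. No data collection, sample size or patient procedure changes.
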